### Final report

The results of the study will be evaluated and discussed and a final report presented to the Federación Diabetológica Colombiana (FDC), entity that is sponsoring the project. The results will be submitted for publication and presented in congresses and scientific meetings.

### Ethical aspects

This study will be conducted in accordance with the Declaration of Helsinki and with the Colombian legislation as per the Resolution 8430/93 from the Ministry of Health. Prior to the admission of the patients in the study, the objectives and the methodology will be explained and a written informed consent obtained. The study was approved by the Research Ethic Committee of the FCV (Act# 075/April 27/2004). The patients' right to confidentiality will be maintained in all the phases of the study.

### Evaluation and management of adverse events

During the visits the patients will be asked about adverse events. Each adverse event will be classified by the physician as serious or non-serious. A serious adverse event should meet one or more of the following criteria:

1. Death

2. Life-threatening

3. Hospitalization or prolongation of existing hospitalization

4. Persistent or significant disability/incapacity

The presence of a serious adverse event that puts the patient's life at risk and/or requires immediate medical or surgical procedure will call for the discontinuation of the treatment and the initiation of the pertinent medical management. The investigator will notify the Adverse Event Committee (AEC) of the FCV of any serious adverse event within 24 hours of learning about it.

A non-serious adverse event will be classified as follows:

1. Mild: The patient is aware of his/her symptoms and/or signs, but those are tolerable. Medical intervention or specific treatment is not required.

2. Moderate: The patients present troubles that interfere with his/her daily activities. Medical intervention or specific treatment is required.

3. Severe: The patient is unable to work or to attend his/her daily activities. Medical intervention or specific treatment is required.

The possible relationship between the adverse events and the tested medication will be classified by the investigator on the basis of his/her clinical judgment and the following definitions:

1. Definitely related: Event can be fully explained by the administration of the tested medication.

2. Probably related: Event is most likely to be explained by the administration of the tested medication rather than other medications or by the patient's clinical state.

3. Possibly related: Event may be explained by the administration of the tested medication or other medications or by the patient's clinical state.

4. Not related: Event is most likely to be explained by the patient's clinical state or by the use of other medications, rather than the tested one.

All the events will be reported to the AEC that, depending on its criteria, will decide the continuity of the patient in the study and therefore the breaking of the code. Although the project has been designed to minimize the inherent risks, any adverse event related to the study medication will be carefully evaluated by the AEC and the costs generated by the required treatment covered by the study.

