### Endpoints

At the end of the treatment the following endpoints will be evaluated:

1. Ulcer reduction percentage.

2. Complete cure of the infection that was present before the treatment.

3. Infection of the ulcers during the treatment.

4. Presence of adverse events related to the application of the patches.

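### 'Not related' requires only that another cause is likelier than the patch, so it overlaps 'Possibly related' with no tie-break

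*Protocol article*

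**What the plan says.** The section Evaluation and management of adverse events in the protocol article gives four causality classes, each defined in a sentence. The investigator assigns them "on the basis of his/her clinical judgment and the following definitions". Three matter here:

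- Probably related, where the patch is the leading cause: "Event is most likely to be explained by the administration of the tested medication rather than other medications".
- Possibly related, where no cause is put first: "Event may be explained by the administration of the tested medication or other medications or by the patient's clinical state".
- Not related, where the leading cause is something else than the patch: "Event is most likely to be explained by the patient's clinical state or by the use of other medications".

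The classification is used in two places. The fourth item under Endpoints is "Presence of adverse events related to the application of the patches". The adverse event section also attaches a consequence to relatedness, at the trial's expense: "any adverse event related to the study medication will be carefully evaluated by the AEC and the costs generated by the required treatment covered". Reporting, in contrast, does not depend on the class: "All the events will be reported to the AEC".

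**The concern.** A 'Not related' class normally holds events that the treatment is not thought to have contributed to. Here it holds events for which something else is merely the likelier explanation. In patients with diabetes and an open foot ulcer, the underlying condition will often be the likelier explanation of local pain, redness or maceration, even where the patch could well have contributed.

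Two consequences follow. Two investigators can apply the definitions faithfully and code the same event on opposite sides of the line between related and not related. And an investigator who follows the wording of the last class literally can place modest, undistinctive patch harm in 'Not related'. The count of related events may then be too low, and the committee evaluation and cost cover worded for related events may not be applied to some participants. An analysis plan can choose which classes to count, but it cannot repair codes already assigned under an ambiguous rule.

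**Working it through.** The article gives no figure for causality coding, so there is none to reproduce. The check has two parts.

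**The definitions side by side.** Take an event for which the patch is a plausible cause but not the leading one.

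- Test for 'Possibly related': could the patch explain it? Yes. The definition sets no lower limit on likelihood.
- Test for 'Not related': is something else the most likely explanation? Yes. The definition does not ask whether the patch can be excluded.
- Tie-break: none is stated, and there is no 'unlikely' class between the two.

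If the scale is instead read as ordered and exclusive, 'Probably related' takes events most likely due to the patch and 'Not related' takes events most likely due to something else. 'Possibly related' then shrinks to near-ties, and the event above falls in 'Not related'. So one reading makes the coding unreliable and the other makes it under-inclusive.

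**How strong an effect the wording can leave in 'Not related'.** Inputs:

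- Allocation 1:1, 50 per group (Sample size).
- Double blind (Methods and design).
- Assumption: 'most likely' means a probability above 0.5. The definition pools clinical state and other medications against the patch, so there are two sides.
- Assumption: the event has no individual features separating it from background and is judged on probability alone, and the patch prevents none of the same events.
- Assumption: RR, the risk of the event with the active patch relative to placebo, is varied from 1.1 to 3.5. The article gives no adverse event rates.

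With n patients per arm and background risk b, placebo yields nb events and the active arm nb × RR, of which nb(RR − 1) are due to the patch.

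- Arm known, active: P(due to patch) = (RR − 1)/RR.
- Arm unknown, 1:1: P(due to patch) = (RR − 1)/(RR + 1).

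Neither depends on b.

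| RR | Active arm known | Blinded, 1:1 |
|---|---|---|
| 1.1 | 0.09 | 0.05 |
| 1.5 | 0.33 | 0.20 |
| 1.9 | 0.47 | 0.31 |
| 2.0 | 0.50 | 0.33 |
| 2.5 | 0.60 | 0.43 |
| 3.0 | 0.67 | 0.50 |
| 3.5 | 0.71 | 0.56 |

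Setting each formula to 0.5 gives RR = 2 with the arm known and RR = 3 under blinding. Below those values, background is the likelier explanation of every such event.

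Illustration with an assumed background risk of 20% and RR 1.5: 50 × 0.20 = 10 events on placebo and 50 × 0.30 = 15 on the patch, an excess of 5. The chance that a given event is due to the patch is 5/15 = 0.33 with the arm known and 5/25 = 0.20 under blinding. All 15 active-arm events meet the wording of 'Not related', and all 15 may also meet 'Possibly related'.

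**The case against.** The strongest case against has five parts.

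*The classes form an ordered scale.* 'Possibly related' names all three causes and favours none, so it can be read as the undetermined grade between two 'most likely' grades. Read with no upper limit it would overlap 'Probably related' as well. This is a fair reading, and it removes the overlap. It does not remove the defect, because a plausible but secondary patch cause then goes to 'Not related'.

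*Events are not coded by group probabilities.* A reader might infer that any patch harm which less than doubles a background event will be classed 'Not related'. The article does not support that. Clinical judgment applies alongside the definitions, and site, timing or recurrence on reapplication can make the patch the leading cause of an event at any RR. A reader might also infer from the illustration that the related count would be 0 in both arms. Where the classes overlap, the wording permits that result but does not produce it. Nor may the assumption that the patch prevents none of the same events hold for infection, since the Background credits nitric oxide with a microbicidal effect.

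*The endpoint may not move.* The Endpoints section does not say which classes count as related. If only the two strongest do, shifting events between 'Possibly related' and 'Not related' leaves that endpoint unchanged. This stands, so the effect on the endpoint is conditional.

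*Harm is captured elsewhere.* All events go to the Adverse Event Committee, the two interim analyses compare safety between groups, and infection of the ulcer during treatment is a separate endpoint with no causality filter. It would be wrong to infer that harm goes unseen. But none of these routes settles the boundary between the two classes.

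*Coding rules may exist elsewhere.* The Logistic phase provides for a procedures manual, a case report form and staff training, and a tie-break could be there. That is possible, but the four definitions are printed as the ones investigators are to apply, and the 'Not related' definition is too wide as printed.

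**Conclusion.** The point holds as a defect in a stated rule. 'Not related' does not require a patch contribution to be unlikely or excluded. An event with a plausible but secondary patch cause can be coded 'Not related', or coded differently by two investigators.

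The RR thresholds of 2 (arm known) and 3 (blinded, 1:1) mark the most that the wording permits for undistinctive events, under the assumptions listed above. They do not predict how events will be coded, and distinctive local reactions lie outside them.

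What is affected is the adverse event endpoint, if 'Possibly related' counts as related, and the committee evaluation and cost cover worded for related events. Because the other safety routes remain open, this is an inexpensive improvement that should be made. It does not threaten the trial's main conclusions.

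**What to change.** In the section Evaluation and management of adverse events, and in the case report form instructions:

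1. Define 'Not related' as no reasonable possibility that the patch caused or contributed to the event.
2. State that any event with a plausible patch cause is at least 'Possibly related', even where another cause is likelier. With item 1, this makes the two classes mutually exclusive.
3. State that all adverse events are compared by arm regardless of attribution.

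The cost is a few sentences of text. Visits, treatment and sample size are unchanged. The downside is that more events will be coded 'Possibly related' in both arms, so that class will discriminate less and the related count will look slightly less favourable. Item 3 offsets this, because a randomised comparison does not depend on the causality code. It should be reported as an estimate with its confidence interval and not relied on as a test: in the illustration (20% against 30%, 50 per arm) its power is only about 21%.

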## Methods and design

Double blind, randomized, placebo controlled clinical trial.

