### Sample size

The sample was calculated according to the arccosine formula considering a power of 80% and a type I error of 0.05. Assigning a successful rate of 30% in the control group and 60% in the active group, 95 participants will be needed. After adjusting for a loss rate of 5%, the total number of patients that must be recruited is 100 (50 patients per group).

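### The adverse event committee's ruling on an event decides whether the patient stays in the study, and the code break follows from it; this risks outcome-related loss of ulcer measurements and unblinding without need

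*Protocol article*

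**What the plan says.** All of this comes from the protocol article.

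- Methods and design describes the trial as "Double blind, randomized, placebo controlled clinical trial".
- Evaluation and management of adverse events sets an immediate rule for a serious event that threatens life or needs an urgent procedure: it "will call for the discontinuation of the treatment and the initiation of the pertinent medical management". That sentence concerns treatment only.
- Later in the same section, after the severity and relatedness definitions, comes the committee's role. Its input is given as "All the events will be reported to the AEC that, depending on its criteria": every event counts, whatever its seriousness, severity or relatedness. On that input the committee "will decide the continuity of the patient in the study and therefore the breaking of the code". The decision is about the study, and the word *therefore* makes the code break follow from it.
- Endpoints opens with "At the end of the treatment the following endpoints will be evaluated". The four items include "Infection of the ulcers during the treatment" and "Presence of adverse events related to the application of the patches".
- Table 1 schedules ulcer measurement at every visit and photographs from the initial visit to day 90. Final visit allows an earlier date when the ulcer has healed completely.

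**The concern.** Stopping the patch and leaving the study have different statistical consequences. A patient who stops the patch can still be measured at day 90. A patient taken out of the study, on a literal reading, either has no day-90 measurement or has one taken early, when the patch was stopped.

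The trigger is also not independent of the outcome. Ulcer infection and patch-related events are endpoints in their own right, and the Background says that infection impairs wound healing. Patients removed for such events are likely to be healing worse than those who stay. If the patch causes or prevents events, removal will differ between arms. An analysis plan written later can choose how to handle missing values, but it cannot recover measurements that were never taken.

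The second issue is the code. Breaking it for a safety need is normal practice. Here it follows from the continuity decision, whether or not anyone needs the assignment to manage the patient.

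**Working it through.** **Inputs.** From Sample size: success 30% (control) and 60% (active), power 80%, type I error 0.05, 95 patients needed, 5% loss, 100 recruited, 50 per group. The article gives no rate of removal for adverse events, so 5% to 20% is assumed below. Two-sided testing is also assumed.

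**1. The plan's own figure.** With h = 2·asin(√0.60) − 2·asin(√0.30), n per arm = 2·((1.96 + 0.842)/h)² = 41.8, or 84 in total. With a continuity correction, n′ = (n/4)·(1 + √(1 + 4/(0.30·n)))² = 48.23 per arm, or 96.5 in total, close to the stated 95. The loss step reproduces: 95/0.95 = 100. The sample size is not in dispute.

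**2. One arm loses 5 patients, all unhealed and left out of the analysis.**

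- Active arm under the planned effect: 30/50 = 60% becomes 30/45 = 66.7%. The difference goes from 30 to 66.7 − 30 = 36.7 points.
- Control arm under the planned effect: 15/50 = 30% becomes 15/45 = 33.3%. The difference goes from 30 to 60 − 33.3 = 26.7 points.

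The sign of the bias depends on which arm loses patients, and the article does not settle that.

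**3. No true effect, removal from the active arm only.** Both arms truly have 30%. A share r of the active arm is removed, all unhealed, so its apparent rate is pₐ = 0.30/(1 − r) in 50(1 − r) patients. With d = pₐ − 0.30, SE₀ the pooled and SE₁ the unpooled standard error, the approximate rejection rate is Φ((d − 1.96·SE₀)/SE₁) + Φ((−d − 1.96·SE₀)/SE₁).

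Worked at r = 10%: pₐ = 0.333 in 45 patients, pooled rate 30/95 = 0.316, SE₀ = 0.0955, SE₁ = 0.0956. The two terms are 0.054 and 0.011, which sum to 0.064.

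| Removed, r | Apparent active rate | Rejection rate (nominal 0.05) |
|---|---|---|
| 5% | 31.6% | 0.053 |
| 10% | 33.3% | 0.064 |
| 15% | 35.3% | 0.085 |
| 20% | 37.5% | 0.117 |

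**4. Equal removal from both arms, unrelated to outcome.** For 30% v 60%, power is 0.866 with 50 per arm. It falls to 0.848, 0.828, 0.805 and 0.780 at 5%, 10%, 15% and 20% removal. Lost numbers alone matter little. Selective loss is the problem, and recruiting more patients does not correct it.

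**5. Limit of the illustration.** Steps 2 and 3 use the binary success rate from Sample size. The first listed endpoint is percentage ulcer reduction, and these figures do not show how far that would move.

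**The case against.** The best defence is that a safety committee ruling on continuation, with a patient-level code break, is ordinary in a double-blind trial. Reporting all events fixes what the committee sees; it does not make every event a ground for removal. The article nowhere says that a removed patient misses the final visit or is left out of the analysis, and such details commonly sit in a full protocol or analysis plan. An infection or related event that prompted the ruling has already happened, so removal does not erase it.

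Much of this stands. It means the bias is a risk and not a demonstrated effect, and that the absence of a named analysis population is no fault here. It does not remove the point, because the article states a rule that joins study exit and code break. Followed literally, that rule ends later ulcer measurement for the patients it selects.

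Three stronger readings are tempting and are not supported:

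- **That ulcer assessors are unblinded.** The article does not say who learns the code. If measurement of that patient has ended, breaking that patient's code cannot bias it.
- **That the 5% allowance leaves no room for such withdrawals.** Sample size gives a general loss rate and does not define it.
- **That the treatment sentence and the continuity sentence contradict each other.** One is an immediate action for a grave event and the other a committee review of all events; both can hold. The fault is that their relation is left unstated.

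**Conclusion.** The point holds as a risk built into the stated rule. Study continuity is decided on events that overlap the endpoints or bear on healing, and the code break is made a consequence of that decision. The first can cause outcome-related loss of ulcer measurements that differs by arm. The second can unblind patients when nobody needs the assignment.

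Neither the size nor the direction can be derived from the article. If all removed patients are unhealed, all come from one arm and all are left out of the analysis, 5 of 50 shifts that arm by 3 to 7 percentage points. With no true effect and 5% to 20% removed from the active arm, the false-positive rate would be about 0.053 to 0.117. With fewer removals, balanced removals or continued measurement, the effect would be smaller or absent. The rule should be reworded, because doing so is cheap and the lost data could not be recovered later.

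**What to change.** Leave the committee's clinical decisions unchanged. Reword Evaluation and management of adverse events so that three decisions stand apart and their relation is stated:

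1. **Stopping the patch.** A patient who stops and consents to further follow-up continues the Table 1 visits to day 90, with ulcer measurement and photograph, and is analysed in the assigned group.
2. **Leaving the study.** This is recorded separately from stopping the patch, with its reason. If a binary healing outcome is analysed, an unmeasured patient can be counted as not healed. That rule does not fit percentage ulcer reduction, which needs its own.
3. **Breaking the code.** It is broken only when the assignment must be known, not automatically after a continuity decision. The result is withheld from staff who measure ulcers or judge relatedness.

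The cost is protocol wording and a few follow-up visits that are already scheduled. The downside is a slight dilution of the effect, because patients who stopped the patch remain in their assigned group.
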